## Abstract

**Introduction:**

High-intensity interval training (HIIT) is an effective strategy for improving a variety of health and fitness outcomes within school settings. Incorporating HIIT into existing physical activity opportunities appears practically feasible, yet the process evaluation and effectiveness of this strategy needs to be further evaluated. Therefore, a *PRO-HIIT* intervention will be conducted to evaluate the effectiveness of a 12-week school-based HIIT intervention on cardiorespiratory fitness, physical activity, body composition, muscular strength, bone health, cognitive function, wellbeing and academic performance among 12–13-year-olds.

**Methods and analysis:**

Eight classes of year 7 students (12–13-year-olds) from a secondary school in Ningbo, China, will be recruited and randomly allocated into an intervention or control group. While the control group maintains their usual activities, a 6 to 10 min HIIT session will be embedded in the physical education or physical activity lessons five days a week for 12 weeks for the intervention group. Training workshops will be conducted for participants, teachers, and research staff for facilitating the intervention. Outcome data will be collected at three time points: pre- and post-intervention, and two months (summer holiday) upon completion of the intervention. Linear mixed models will be used to analyse the impact of groups (intervention and control), timepoints (pre-, post- and two-month after intervention) and group by time interactions. The implementation process of the intervention will be evaluated using a process evaluation framework.

**Ethics and dissemination:**

Ethics approval is obtained from the Ningbo University Ethics Committee (TY2024002). Results from *PRO-*HIIT study will be disseminated via peer-reviewed journals, scientific conferences as well as local education system. The study protocol has been retrospectively registered on ClinicalTrials.gov Protocol Registration and Results System (NCT06374732), https://clinicaltrials.gov/study/NCT06374732.

## Introduction

Physical activity (PA) is well documented for its role to promote physical fitness and mental wellbeing in children and adolescents (1–4). However, less than 20% of adolescents meet the World Health Organization guideline for engaging in an average of 60 min of daily moderate to vigorous PA across the week (3). The most cited barriers for adhering to the recommendations include time constraints, lack of motivation and inadequate facilities (5, 6). Notably, engaging in vigorous PA is of salient health significance for children and adolescents. Vigorous PA has been independently associated with lower levels of cardiometabolic risk factors, higher cardiorespiratory fitness (CRF) and improved bone health in this population (7, 8). With time constraints for PA participation among young population, prioritising vigorous PA by employing high-intensity interval training (HIIT) might be a viable option for health promotion (9). HIIT, featuring short bursts of intense exercises interspersed with active recoveries or rests, has emerged as a time-efficient and effective exercise strategy for children and adolescents (5, 10).

Schools act as the ideal settings for PA programmes because of the abundant resources available within the education system, such as staff, space and facilities, different timing options (e.g., breaks and classes) and broad reach of children and adolescents (1, 11). Time spent in schools account for a significant proportion of children's waking hours, hence these institutions have the potential to counteract the global issues related to physical inactivity (12) and health inequalities (13). In recent years, there has been an interest in integrating HIIT into school settings. Review-based evidence indicates that school-based HIIT interventions effectively enhance body composition (14–16), CRF (15, 16) and muscular health (17). However, the impact on cognitive function and academic performance remains uncertain (15) and evidence regarding its health benefits for mental well-being (15) and bone health (18) is limited.

Despite the advantages of school settings, integration of PA programmes into schools is challenging. This is mainly because of the additional workload imposed on already overworked schoolteachers and the potential diversion of students’ valuable time away from academic study (19). One practical solution to address this challenge is to incorporate PA interventions during dedicated curriculum time for PA, such as during physical education (PE) lessons. Lubans et al. (9) proposed that for school-based HIIT to be scalable, it should be integrated into existing PE or sport training sessions. Indeed, a recent review highlighted that 57.1% (*n* = 24) of the 42 identified school-based HIIT interventions were conducted during PE lessons (15). Given that less than 50% of a typical PE lesson time is spent in moderate-to-vigorous PA in secondary school (20), HIIT targeting PE lessons might potentially enhance the quality of PE (21) and health condition of children and adolescents (15, 17, 22, 23).

Recent research has highlighted the risk of fitness loss or stagnation during prolonged and unstructured days (defined as weekends or holidays when obesogenic behaviours are prevalent due to lack of compulsory PA opportunities, restriction on caloric intake, limitation on screen time, and regulated sleep schedules), a phenomenon known as the “Structured Days Hypothesis (SDH)” (24). In supporting the SDH, a survey conducted in Australia demonstrated that children spent more time watching TV or playing videogames and engaged in less PA, leading to a reduced daily energy expenditure during unstructured holidays (25). Martin et al. (26) showcased the efficacy of a 7-week school-based HIIT programme in mitigating potential CRF loss among Scottish adolescents during summer vacation. However, the impact on other health-related factors remains underexplored and their study is limited by a lack of implementation details.

One useful approach to improve the intervention reporting is through conducting a process evaluation. Process evaluation delves into implementation details, mechanisms of impact and contextual factors, offering a comprehensive understanding regarding the intervention effectiveness and underlying causality (27). It runs parallel to the outcome assessment, which contributes to future scaling up and dissemination (23, 27). Nonetheless, only a limited number of school-based HIIT interventions have included process evaluations, either as sections within intervention outcome papers (28, 29) or as standalone pieces (30–32). Among these studies, only two interventions employed a process evaluation framework (30, 32). Conducting process evaluation without proper guidance may pose challenges, potentially leading to incomplete reporting and biased results and interpretations (33).

## Aims of the study

Given the above stated research gaps, the present study aims to conduct a school-based HIIT intervention named *PRO-HIIT.* The *PRO-HIIT* is a health promotion initiative designed to deliver 6–10 min of HIIT into the daily routines of Chinese adolescents, with a focus on settings of existing PA opportunities. Specifically, while the control group will take the usual PE (*n* = 3) and PA lessons (*n* = 2) every week, a 6–10 min of HIIT will be embedded at the beginning of these lessons five times per week for twelve weeks for the intervention group. The aims of the *PRO-HIIT* are to:
(1)evaluate the effectiveness of the *PRO-HIIT* on CRF (primary outcome), PA, body composition, muscular strength, bone health, executive function, wellbeing, enjoyment, motivation, affect, self-efficacy and academic performance among 12–13-year-old adolescents;(2)examine the changes of these outcomes following a two-month unstructured summer holiday after the *PRO-HIIT* study is completed;(3)evaluate the implementation process of the *PRO-HIIT* through a process evaluation.

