## Methods and analysis

### Study design

The study is a multi-centre collaborative work conducted by University of Exeter and Ningbo University. Consolidated Standards of Reporting Trials (34) and Template for Intervention Description and Replication (35) checklists will be adopted for guidance and reporting. The *PRO-HIIT* study will employ a two-arm cluster-randomised controlled trial design, with an intervention group and a treat as usual control group. Clusters in this study are eight classes of secondary school students, located in Ningbo City, China. The intervention will be delivered five times per week, commencing at the beginning of the three PE and two PA lessons. The PA lessons serve as a complementary opportunity for students to engage in exercises of their choice on days when PE lessons are not scheduled. Assessments will occur at three time points: baseline (T1), immediate post-intervention (T2) and two-month post-intervention (T3), with T3 aligning with the initial two weeks of a new school term following a two-month unstructured summer holiday. Table 1 presents an overview of the schedule for recruitment, intervention delivery and outcome assessments.

**Table 1 T1:** Overview of the *PRO-HIIT* intervention.

Procedures		Recruitment & pre-intervention measurements				Intervention phase (12 weeks)												Post-intervention measurements			Summer holiday	Follow-up measurements	
	22–26 Jan	26 Feb–22 Mar				25 Mar–14 Jun												17–28 Jun		1–4 Jul	5 Jul–1 Sep	2–13 Sep	
	2023–2024 school term 1	2023–2024 school term 2																				2024–2025 school term 1	
	week 22	week 1	week 2	week 3	week 4	week 5	week 6	week 7	week 8	week 9	week 10	week 11	week 12	week 13	week 14	week 15	week 16	week 17	week 18	week 19		week 1	week 2
Eligibility screening		√																					
Consents & assents																							
Training workshop			√																				
Randomisation					√																		
Maturity				√																			
PA (GENEActiv)					√	√											√	√					
PA (questionnaire)				√														√				√	
Sleep																							
Body composition																							
CRF																							
Muscular strength																							
Bone health																							
Executive function																							
Wellbeing																							
Enjoyment																							
Motivation																							
Affect																							
Self-efficacy																							
Academic assessment	√																			√			

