### Outcome measurements

Outcome measurements will be conducted in the school premises by trained research assistants who will remain blinded to group allocation throughout all assessment time-points. All measurements will be introduced and explained during the training workshop and will be described again prior to the commencement of the measurements to ensure clarity. The measurements will be conducted during their regular PE lessons. Details of the outcome measures are summarised in Table 5.

**Table 5 T5:** How, when and where the outcome variables will be measured.

Outcomes	Tools	Timing	How and where (all participants, measured at class level)
Physical activity	GENEActiv	One week before and after intervention, first and last week of intervention.	A subsample of 60 participants (30 in each group, 30 males) will be randomly selected to wear the GENEActive accelerometer for 14 days consecutively for twice, covering the total 4 weeks.
Cardiorespiratory fitness	20 m shuttle run	T1, T2, T3	Multiple measurement stations will be held, and participants will be split into groups to ensure efficient measurements. Two physical education lessons are estimated to be sufficient. All these measurements will be conducted in sports hall.
Body composition	TANITA	T1, T2, T3	
Muscular strength	Handgrip, standing long jump	T1, T2, T3	
Bone health	GE Achilles	T1, T2, T3	
Executive function	Flanker tasks, visual 2-back tasks, colour-shape switch tasks	T1, T2, T3	Perform the executive function tasks online in a school computer room in one physical education lesson (40 min).
Wellbeing	SDQ	T1, T2, T3	Finish together using one physical education lesson (40 min) in a school computer room with the instruction of research staff.
Enjoyment	PACES	T1, T2, T3	
Motivation	BREQ-2	T1, T2, T3	
Affect	PANAS-SF	T1, T2, T3	
Self-efficacy	PPAS	T1, T2, T3	
Academic performance	End-of-term academic examinations	By the end of term 1 and T2	Obtained directly from head teacher.

SDQ, strength and difficulty questionnaire; PACES, physical activity enjoyment scale; BREQ-2, exercise regulations questionnaire; PANAS-SF, positive and negative affect schedule short form; PPAS, perceived physical ability scale; T1, pre-intervention; T2, immediately post-intervention; T3, 2-month follow-up.

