#### Secondary outcomes

##### Physical activity

For a subset of randomly selected (stratified by sex and group) participants (*n* = 60), PA will be objectively assessed using GENEActiv wrist-worn accelerometers (Model GAT04, Activinsights Ltd, Cambridgeshire, England) over a span of four weeks, comprising one week before and after the intervention as well as the initial and concluding weeks of the intervention. Participants will be encouraged to wear the device 24 h/day, without taking off even when bathing or sleeping. GENEActive accelerometers have demonstrated acceptable reliability and validity for PA monitoring in adolescents (44). The cut-points employed to categorise sedentary, light, moderate and vigorous PA are <6, 6–21, 22–56, and >56 g s, respectively (44).

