##### Confounding variables

An estimate of the age of peak height velocity will be used to assess the somatic maturation of participants (59). Participants’ PA and sleep at all time-points will be assessed by a Chinese version of the International Physical Activity Questionnaire, short form (IPAQ-SF) (60) and a validated Chinese version of the Pittsburgh Sleep Quality Index (PSQI) (61), respectively.

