#### Statistical analyses

Data entry will be completed by one researcher with a random sample of at least 10% of entries cross-checked by a second researcher for accuracy. Prior to analysis, thorough checks for outliers and errors will be conducted using range and boxplot methods. Additionally, assessments for normality, homogeneity of variances and sphericity will be conducted as needed to verify assumptions. The baseline data for intervention and control groups will be presented and compared at individual level using independent sample *t*-test. An intention-to-treat approach will be adopted to evaluate the effects on outcome variables to avoid bias in exploring the impact of the intervention. Linear mixed-effect models will be used, with random effects, to analyse the impact of groups (intervention and control), timepoints (pre-, post-intervention and follow-up) and group × time interactions. Statistical analyses will be adjusted for the clustering effects at class level. Per protocol sensitivity analysis will be undertaken at the class level. Considering for disruptions such as school holidays, exams, severe weather, a minimum of 30 sessions is considered achievable over the 12-week period. Other sensitivity analyses, such as complete-case analysis, will be conducted where appropriate. Moderators, including sex (male, female), baseline overweight/obese (yes, no) and baseline CRF (healthy vs. needs to improve), will be examined with linear mixed models. Where appropriate, subgroup analyses will be conducted for the significant group-by-moderator interactions. PA, sleep and maturity will be included in the model to eliminate confounding effects. All data analyses will be conducted via IBM SPSS Statistics for Windows (SPSS 28.0; IBM Corporation, Armonk, NY, USA), with an alpha level of 0.05.

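### Aim 2 covers physical activity after the summer holiday, but the plan yields no PA outcome at T3: accelerometry ends in week 17 and the T3 questionnaire is listed only as a confounder

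*Protocol article*

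**What the plan says.** **The aims.** In the protocol article, Aims of the study, aim 1 lists the outcomes, beginning "CRF (primary outcome), PA, body composition, muscular strength, bone health". Aim 2 is to "examine the changes of these outcomes following a two-month unstructured summer holiday". The Study design section defines the follow-up assessment, "with T3 aligning with the initial two weeks of a new school term following a two-month unstructured summer holiday".

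**The PA outcome.** Table 5 gives one tool for PA, the GENEActiv accelerometer, timed "One week before and after intervention, first and last week of intervention" and worn for "14 days consecutively for twice, covering the total 4 weeks" by 60 randomly selected participants. The Physical activity section, under secondary outcomes, describes the same four weeks: "comprising one week before and after the intervention as well as the initial and concluding weeks of the intervention". Table 1 ticks the accelerometer in weeks 4, 5, 16 and 17, with nothing in the follow-up columns.

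**The activity questionnaire.** Table 1 has a separate row for PA by questionnaire, ticked in week 3, week 17 and the first follow-up week. The text describing it stands under Confounding variables, where participants' PA and "sleep at all time-points will be assessed by a Chinese version of the International Physical Activity Questionnaire, short form (IPAQ-SF"). Table 5 does not list it as an outcome tool. Under Statistical analyses the relevant sentence is "PA, sleep and maturity will be included in the model to eliminate confounding effects".

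**A declared exception.** The Academic performance section states that this outcome is not measured at follow-up. No such statement is made for PA.

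**The concern.** A stated aim and the measurement plan do not meet. Aim 2 takes in every outcome of aim 1, so it takes in PA. Yet the measure designated as the PA outcome stops before the holiday begins, and the measure that does reach T3 is designated as something else. An analyst following the text would report no PA change across the holiday and would not be told that this was intended.

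The role given to the questionnaire raises a second issue. PA appears both as an outcome the intervention may change and as a confounder to be adjusted for. PA measured before randomisation is a proper baseline covariate. PA measured after allocation cannot confound a randomised comparison and may lie on the path from the intervention to fitness. Adjusting for it could distort the group-by-time estimates, including the one for CRF, the primary outcome.

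**Working it through.** The point concerns roles and timing, so the check sets the sections side by side.

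| PA measure | Who | Weeks (Table 1) | At T3? | Stated role |
|---|---|---|---|---|
| GENEActiv | 60 sampled | 4, 5, 16, 17 | No | Secondary outcome (Table 5; Physical activity) |
| IPAQ-SF | Participants, no subset stated | 3, 17, first follow-up week | Yes | Confounder (Confounding variables; Statistical analyses) |

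**Step 1: does aim 2 include PA?** Yes. It refers back to the aim 1 list, where PA follows CRF directly.

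**Step 2: when does the PA outcome end?** Table 1 starts school week 1 on 26 February 2024. Week 17 therefore starts 16 × 7 = 112 days later, on 17 June, and ends on 23 June. The holiday runs from 5 July to 1 September, and T3 from 2 to 13 September.
- 23 June to 5 July: 7 + 5 = 12 days.
- 23 June to 2 September: 7 + 31 + 31 + 2 = 71 days.
- Accelerometer wear: 2 × 14 = 28 days, or 4 weeks, of which 0 fall at or after the holiday.

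This does not rest on how Table 1 was extracted, because Table 5 and the Physical activity section give the same four weeks in words.

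**Step 3: is another PA outcome analysed at T3?** None is stated. The IPAQ-SF is collected then, but the only use described is adjustment.

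**Step 4: what data are scheduled?** Eight classes of about 50 give 8 × 50 = 400 pupils. If the sample-size section's 20% dropout applied in full by T3 (an assumption), 400 × 0.8 = 320 would have a scheduled follow-up questionnaire. This counts scheduled data and is not a statement about power.

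**Step 5: which PA value is adjusted for?** Recruitment and allocation places randomisation after baseline assessment. Table 1 agrees, with the questionnaire in week 3 and randomisation in week 4. The T1 value is therefore pre-randomisation, and the T2 and T3 values are post-randomisation. The analysis section names neither the instrument nor the time point. The IPAQ-SF is the natural reading, since it is the measure listed as a confounder and the accelerometer covers only 60 pupils. Because it is collected at every assessment and the model has three time points, time-varying adjustment is open to the analyst, but the text does not state it.

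No sample-size or error-rate figure in the article depends on any of these steps.

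**The case against.** The strongest reply is that this is a labelling mismatch on one secondary outcome and that the schedule is not hidden: Table 5 gives PA its own timing, distinct from T1, T2, T3. Several parts of that reply stand.

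- **The data exist.** A reader might infer that the PA part of aim 2 cannot be answered at all. The documents do not support that. The questionnaire is scheduled at T1, T2 and T3, so the gap is in the analysis plan and not in data collection.
- **T3 follows the holiday.** A reader might infer that a measure of holiday activity is being lost. No outcome is scheduled within the holiday, and aim 2 promises only change after it.
- **The Structured Days Hypothesis is wider than activity.** A reader might infer that the trial cannot address it without PA at T3. The Introduction also names caloric intake, screen time and sleep schedules, and the Discussion frames the contribution as fitness loss. CRF, body composition and strength are all measured at T3.
- **Time-varying adjustment is not stated.** Maturity, in the same list of covariates, is ticked only in week 3, and the form of each covariate may be settled in an analysis plan that is not shown.

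What does not stand is the suggestion that visible timing in the tables removes the conflict. Aim 2 still includes PA, and the article shows with academic performance how it declares an exception when it means one. Nor does silence on the covariate's timing make the sentence safe: it gives confounding as the reason for adjustment, a reason that can apply only to the pre-randomisation value.

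**Conclusion.** The point holds as a conflict between aim 2 and the stated outcome and analysis roles. The plan as written gives no PA outcome result at T3, because none of the four accelerometer weeks reaches it and the questionnaire that does is assigned only to adjustment. The self-report data needed to supply a result are already scheduled.

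The adjustment point is conditional. If only the T1 value enters the models, there is no problem. If T2 and T3 values enter, the models condition on a post-randomisation variable that is itself a listed outcome, and effect estimates, including that on CRF, could be biased. The article gives nothing from which to estimate the size of that bias.

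This should be corrected, but it does not touch collection of the primary outcome or the sample size. The conclusion assumes that the PA covariate is the IPAQ-SF and that the questionnaire is given to all participants, as the Confounding variables section implies.

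**What to change.** 1. **Resolve aim 2 in one of two ways.** Either name IPAQ-SF activity at T1, T2 and T3, in all pupils, as the PA outcome for aim 2, and state that it is self-reported and a different instrument from the accelerometer used in the subsample; or restate aim 2 to exclude PA, as is already done for academic performance.
2. **Fix the covariate.** State under Statistical analyses that only the T1 IPAQ-SF value is used for adjustment in the models for other outcomes. If IPAQ-SF becomes an outcome, its T2 and T3 values must not also appear as covariates in its own model.

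Both are wording changes to the aims, outcome and analysis sections and need no new measurement. The cost of the first option is that the follow-up PA result rests on self-report and is not directly comparable with the accelerometer result. The cost of the second is that the trial reports no PA result at follow-up.
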